## 1. Introduction

The most prevalent infection in the intensive care unit (ICU) is the hospital–acquired pneumonia (HAP) [1,2]. This group of conditions encompasses two different entities: ventilator-associated pneumonia (VAP) and high-severity pneumonia developed during hospitalization. VAP is a type of pneumonia that develops in mechanically ventilated patients. The reported incidence of VAP is extensive, ranging from 1.9–3.8 per 1000 days of mechanical ventilation in the USA to more than 18 per 1000 days in Europe [1]. The incidence of this type of pneumonia in Romania is probably even higher, but retrospective or prospective multicentric studies have not quantified its prevalence [2].

VAP occurs after 48 h of mechanical ventilation. The onset relative to hospital admission discriminates early pneumonia (under five days) from late pneumonia (over five days) [3,4].

VAP diagnosis is made on clinical, paraclinical, and radiological criteria. For the radiological criterion to be met, two successive chest radiographs showing new or progressive lung infiltrates or a single chest radiograph without a medical history of underlying heart or lung disease are required. It should be accompanied by at least one of the following: new onset fever (without any other cause) or changes in the leukocytes number (≤4000 mm^3^ or ≥12,000 mm^3^) and at least two of the following signs: purulent sputum, (cough, dyspnoea—for HAP), declining oxygenation, increased oxygen requirements(4).

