## 2. Methods

The present study is a prospective, observational, single-center study. It aims to isolate the bacteria in the biofilms of the tracheal cannulas of mechanically ventilated patients. The purpose of bacterial isolation is not only to compare with the bacterial load from tracheobronchial secretion but also to determine the optimal replacement time of the endotracheal cannulas in patients with prolonged mechanical ventilation.

It is estimated that more than 100 mechanically ventilated patients will be enrolled in the study over 12 to 18 months. The study will be located in the intensive care unit of Sibiu County Clinical Emergency Hospital, Romania. This ICU is a level I intensive care as it can assist a large variety of pathology: medical and surgical (general, thoracic and vascular surgery, neurosurgery, ENT, urology, trauma, and burns). It is organized on two floors with 12 single-bed rooms on each floor and four double-bed rooms for post-anesthesia care/intermediary care. 

This study will not affect the patient’s treatment plan and will be performed according to the attending physician’s indications. The endotracheal cannulas will be replaced if the patient’s clinical assessment allows this maneuver without endangering the well-being of the ill.

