### 2.1. Aims of the Study

Detection of the bacteria in the biofilm formed inside the endotracheal cannulae.

Detection of the mean period during which the biofilm organizes in the lumen of the cannulae.

Determination of the optimal time to replace the intubation cannulae in patients that need mechanical ventilation for more than 48 h so that the contamination of the lower respiratory airways by dislodging the biofilm following suction maneuvres is prevented. 

Comparison of the microorganisms from the patient’s respiratory secretions with the bacterial load in the biofilm to initiate an early targeted antibiotherapy. Furthermore, it should be determined whether a clean cannula with a sterile biofilm can prevent the onset of VAP. 

Development of new methods to prevent VAP.

Final aim: decreasing the morbidity and mortality of critically ill patients by preventing or early and targeted treating VAP, reducing the LOS in the ICU and in the hospital with a secondary lowering of costs associated with hospitalization.

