### 2.5. Microbiological Specimens—The Timing of the Sampling, Specimen Manipulation, Sonication Protocol

T_0_: tracheal aspirate collection in the first 2 h after the patient’s admission to the intensive care unit or after tracheal intubation and initiation of the invasive respiratory support.

Collection of a second tracheal aspirate 48–72 h after T_0_.

Replacement of the endotracheal cannula at 48–72 h from T_0_ and collection of a cannula specimen. The specimen will be sonicated according to an established protocol for bacterial sonication, and the sonication fluid will be inoculated onto bacterial culture media.

Collection of a third tracheal aspirate at 168–192 h from T_0_ if the patient requires prolonged mechanical ventilation or required reintubation less than 24 h from the time of extubation.

Change of the endotracheal cannula at 168–192 h from T_0_ and the collection of the cannula specimen, sonication, and fluid seeding onto growth media.

Sonication protocol: Orotracheal intubation cannula specimens will be sonicated for 30 min using an ultrasonic bath (BactoSonic14.2, Bandelin GmbH, Berlin, Germany) at a frequency of 42 kHz with a power of 0.22 W/cm^2^. The resulting sonication liquid is then homogenized, and 5–10 mL is centrifuged for 5 min at 2500 rpm. The resulting precipitate will be inoculated onto culture media and incubated at 37 degrees to inspect them for bacterial growth.

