As this method progressed in orthopedy, more doctors used sonication to isolate bacteria on the infected knee and hip prostheses. In a recent study, the authors isolated many strains of bacteria. There were found gram-positive bacteria and also gram-negative bacteria with different kinds of resistance to antibiotics. Though the clinical signs and symptoms suggest prosthetic infection, no microorganism could be isolated through classic methods. Using sonication on infected hip or knee prostheses extracted from patients, the authors isolated numerous strains of microorganisms: Coagulase-negative staphylococci (CoNS) species—epidermidis, lentus, xylosus, epidermidis, hominis, hemolyticus; Enterococcus faecalis, Escherichia coli, Klebsiella spp, Proteus mirabilis, Pseudomonas spp and even Acinetobacter spp. Along with sonication, other tissue samples were collected in the intraoperative period: one was used for the histopathological examination, the prosthetic membrane, and the others were sent for bacterial cultures in the microbiology laboratory [31].

For orthopedic patients, to use sonication on the prosthesis, there is a need for genuinely invasive procedures. On the other hand, the invasivity is very low in dentistry, at least in the case of totally mobile dental prostheses. In the intensive care unit, we are between orthopedy and dentistry to get the specimen for sonication, as a piece of the intubation cannula is needed.

As with any diagnostic method, sonication has its limitations. First, the sonication fluid is needed. If the patient is not stable enough (there are difficulties in maintaining proper oxygenation or the cardiovascular system needs increasing vasoactive or positive inotrope support), the tracheal cannula cannot be changed in the proposed timeline without endangering the ill. In this scenario, the cannula will stay on the spot, and the patient will be excluded from the study. Even though it enhances detection sensitivity compared to traditional culture methods, it may cause cell damage and loss of viability, and furthermore, cannot differentiate between viable or nonviable microorganisms.

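### The design cannot determine an optimal cannula replacement time or whether a sterile cannula prevents VAP: there is one exchange schedule, and biofilm status comes only from a tube already removed

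*Protocol article*

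**What the plan says.** Section 2 of the protocol article describes the design: "The present study is a prospective, observational, single-center study". It then names the optimal replacement time as one purpose of isolating the bacteria. Section 2.1 lists this among the aims, "Determination of the optimal time to replace the intubation cannulae in patients that need mechanical ventilation for more than 48 h", and adds that "it should be determined whether a clean cannula with a sterile biofilm can prevent the onset of VAP".

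Section 2.5 gives one sampling schedule. The first exchange is "Replacement of the endotracheal cannula at 48–72 h from T_0_ and collection of a cannula specimen". The second, for patients who remain ventilated, is "Change of the endotracheal cannula at 168–192 h from T_0_ and the collection of the cannula specimen". Colonisation is read from the removed tube: "The specimen will be sonicated according to an established protocol for bacterial sonication", followed by culture of the fluid. If a patient is too unstable for the exchange, the Discussions state that "the cannula will stay on the spot, and the patient will be excluded from the study".

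Section 2.3 groups patients by cause of respiratory failure. Group 1 has confirmed or strongly suspected pulmonary infection at entry. The Introduction states that "VAP occurs after 48 h of mechanical ventilation".

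**The concern.** Both aims ask what would happen under a different course of action. Calling a replacement time optimal requires outcomes under at least two replacement times. Saying that a sterile cannula prevents VAP requires the patient to be exposed to a tube of known status, before VAP starts, with the comparison protected from other differences between patients. The schedule supplies neither.

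If the aims stay as worded, a descriptive result could be reported as support for a replacement interval that was never compared with another. A sterile-versus-colonised difference in VAP could likewise be reported as prevention. The article itself treats the exchange as a manoeuvre that may endanger some patients, so an interval drawn from such data would matter.

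**Working it through.** There is no stated figure to reproduce: the sample size of at least 100 is given without error rates, effect size or event rate. The check is mainly one of setting aims against schedule.

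**1. Contrast in replacement time.** Section 2.5 has one schedule. The Discussions remove patients who could not follow it, and section 2.3 groups by cause of failure. No analysed group has a different planned replacement time or no replacement. Timing within a window does vary, but section 2 makes exchange depend on clinical assessment, so that variation may follow patient stability.

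**2. Cannula ages observed.**
- First cannula: 48–72 h if T0 is intubation. Section 2.5 also allows T0 to be ICU admission, and section 2.4 covers patients who arrive already ventilated, so dwell can be longer.
- Second cannula: shortest 168 − 72 = 96 h; longest 192 − 48 = 144 h, assuming no reintubation in between.

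Each cannula gives one result, at removal. Colonisation can be described in these two bands. The second band contains only patients still alive and ventilated at about 168 h from T0.

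**3. Order of exposure and outcome.** Status is known only after the tube has gone and a new one of unknown status is in place. VAP can begin after 48 h of ventilation, so it may precede or coincide with the first removal, and it has longer to precede the second. An infected patient may colonise the tube, rather than the reverse. Group 1 sharpens this, because pulmonary infection is present or suspected from the start.

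**4. Confounding.** Cause of failure, severity and antibiotic treatment can each influence both the culture result and the risk of VAP.

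**5. Information available for an association.** The Introduction cites VAP in 9–40% of intubated patients. Per 100 patients this is 100 × 0.09 = 9 to 100 × 0.40 = 40 events, before anyone is removed for existing infection.
- Four parameters (colonisation, group, severity, antibiotics): 9/4 ≈ 2 to 40/4 = 10 events each.
- Three parameters (colonisation, group, one severity score): 9/3 = 3 to 40/3 ≈ 13 events each.

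**6. Illustrative power for an association only.** Assumptions not in the article: sterile cannulas carry half the VAP risk, a share s of 20–50% are sterile, two-sided alpha is 0.05, and the normal approximation applies. With overall risk p, the risk with a colonised cannula is p/(1 − 0.5s), and the risk with a sterile one is half of that.

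| At risk | Overall VAP p | s | Risk, colonised | Risk, sterile | Power |
|---|---|---|---|---|---|
| 100 | 9% | 20% | 10.0% | 5.0% | 6% |
| 100 | 25% | 50% | 33.3% | 16.7% | 49% |
| 100 | 40% | 50% | 53.3% | 26.7% | 79% |
| 50 | 9% | 20% | 10.0% | 5.0% | 4% |
| 50 | 25% | 50% | 33.3% | 16.7% | 27% |
| 50 | 40% | 50% | 53.3% | 26.7% | 49% |

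The 50-patient rows assume that half the sample is uninfected at entry. The approximation is poor at the low end. More patients would raise these figures but would not create the contrast missing in step 1.

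**The case against.** The best defence is that the replacement-time aim may be microbiological: section 2.1 links it to contamination from dislodged biofilm and places it after an aim about how long biofilm takes to organise. Colonisation by cannula age would inform that reading, and cannula age does vary. This stands in part. The age question can be described, in two coarse bands, but moving from there to an optimal time still needs outcomes under alternatives.

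A second defence is that landmarks, competing events and adjustment belong in an analysis plan that is not shown. That is fair for the analytic detail. It does not rescue the aims, because no analysis plan can supply a replacement time that nobody received or the status of the tube still in place.

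Third, the Abstract's primary purpose, detecting bacteria before infection is manifest, is untouched, and section 2.1 mixes objectives with aspirations. This limits the severity.

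Two stronger readings are tempting, and the documents do not support them:
- **Immortal-time bias.** A reader might infer it because second-cannula patients must reach about 168 h. Sterile and colonised patients classified at the same exchange share that guaranteed time, so it is selection, limiting to whom the result applies. Bias between the classes would need follow-up from T0 with mixed classification, which the article does not state.
- **A 24 h limit on misordered VAP.** A reader might subtract 48 h from 72 h. That holds only if T0 is the start of ventilation, and only for the first cannula; for the second, the span from 48 h to 192 h is up to 144 h. Nor does the article say that VAP present before removal would be counted as an outcome.

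**Conclusion.** As worded, neither aim can be answered by this observational, single-schedule design. The size is structural: no planned contrast in replacement time, and no patient followed on a cannula whose status is known. Descriptive and associational versions remain possible: colonisation at about 48–72 h or longer and at 96–144 h of dwell, and an exploratory association with later VAP. The association would rest on roughly 9–40 events per 100 patients if the cited 9–40% applies to this unit, and fewer once patients already infected at removal are set aside.

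The conclusion rests on the schedule and the exclusion rule as printed; the power figures are illustration only. The point should be fixed but does not threaten the primary purpose. It does not bear on whether any particular exchange time is right or wrong.

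**What to change.** In sections 2 and 2.1, replace the two aims with:

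1. The proportion of cannulas colonised by actual dwell time, counted from intubation and not only from T0. State that second-cannula results apply to patients still alive and ventilated at about 168 h.
2. An exploratory association between colonisation of the removed cannula and subsequent VAP, among patients free of VAP or pulmonary infection at removal, with follow-up starting at removal. Keep adjustment small, for example group and one severity score (SOFA or APACHE II). Antibiotic exposure can be tabulated by colonisation status and acknowledged as residual confounding.

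Remove the claims to determine an optimal time and to show that a sterile cannula can prevent VAP. If either is wanted as a conclusion, it needs a separate design with a planned contrast.

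Cost: no extra patients or samples. Group, severity scores and antibiotics are already recorded. The time of intubation, including intubation before ICU admission, and the date of VAP onset must be available; section 2.4 as printed lists only days in the ICU before intubation. The claims become more modest. The at-risk set for the second aim shrinks, since much of Group 1 may drop out of it, and the group term may then carry little information.

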### 2.2. Population Description

Patients admitted to our ICU, aged between 18 and 100 years old, are mechanically ventilated for more than 48 h. Among the causes of respiratory failure are pulmonary infections (bacterial, viral, or fungal pneumonia, bronchopneumonia, COPD exacerbations due to respiratory tract infections), aggravated lung diseases (severe asthma attack, status asthmaticus), or extrapulmonary factors (polytrauma after traffic accidents, falls, neurological or neurosurgical patients with deteriorated consciousness and alterations of the airway reflexes).

### 2.3. Inclusion Criteria

Age between 18 and 100 years old.

Romanian citizenship.

Patients or legal representatives are informed and consent in writing to be part of the study.

Patients that require more than 48 h of mechanical respiratory support.

Exclusion criteria:

Under-aged patients.

Patients who do not consent or the consent could not be obtained.

The non-compliant collection of biological samples in patients.

Clinically unstable patients, so the samples could not be collected.

Less than 48 h of mechanical ventilation.

Non-Romanian nationality.

Eligible patients for the proposed research topic will be divided into two groups according to the cause of respiratory failure:

Group 1—respiratory failure due to pulmonary infection—confirmed bacterial pneumonia, bacterial bronchopneumonia, or with a high degree of clinical and biological suspicion (purulent tracheal secretions, paraclinical or imaging investigations highly suggestive of respiratory infection).

Group 2—respiratory failure secondary to non-infectious pulmonary conditions (severe asthma attack, pulmonary fibrosis) or extrapulmonary causes that need mechanical ventilation (polytrauma secondary to traffic accidents, falls, neurological or neurosurgical patients, patients with deteriorated consciousness that need airway protection).

### 2.4. Data Collection

After admission to the ICU, a quick but rigorous clinical exam is performed to stabilize or correct the issues that can immediately endanger the patient’s life, according to the ABC rule (airway, breathing, circulation). If the patient is already mechanically ventilated, the patency of the tube is checked, and specific ventilatory parameters will be set to ensure adequate ventilation and respiration of the critically ill. If the patient breathes spontaneously but needs respiratory support, orotracheal intubation will be performed, and mechanical ventilation will be initiated. The same measures are taken in the case of the patient that is already in the ICU but has deteriorated. 

Data:

Age, gender, BMI.

Length of stay in hospital.

Length of stay in ICU.

Number of days of stay in ICU before intubation.

Outcome.

Mortality at 28 days.

Diagnostic criteria for ICU admission.

Cause of the respiratory failure.

Associated conditions.

Sickness severity scores (SOFA, APACHE II).

Pneumonia severity scores (PSI/Pneumonia severity index; SMART-COP Score; CURB-65).

Blood work (including inflammatory panel and blood gas analysis).

Monitoring curves (blood pressure, heart rate, oxygenation, ventilation, diuresis, GFR, creatinine clearance).

Antibiotherapy.

Newly onset organ dysfunction/worsening of a preexisting organ dysfunction/organ failure.

### 2.5. Microbiological Specimens—The Timing of the Sampling, Specimen Manipulation, Sonication Protocol

T_0_: tracheal aspirate collection in the first 2 h after the patient’s admission to the intensive care unit or after tracheal intubation and initiation of the invasive respiratory support.

Collection of a second tracheal aspirate 48–72 h after T_0_.

Replacement of the endotracheal cannula at 48–72 h from T_0_ and collection of a cannula specimen. The specimen will be sonicated according to an established protocol for bacterial sonication, and the sonication fluid will be inoculated onto bacterial culture media.

Collection of a third tracheal aspirate at 168–192 h from T_0_ if the patient requires prolonged mechanical ventilation or required reintubation less than 24 h from the time of extubation.

Change of the endotracheal cannula at 168–192 h from T_0_ and the collection of the cannula specimen, sonication, and fluid seeding onto growth media.

Sonication protocol: Orotracheal intubation cannula specimens will be sonicated for 30 min using an ultrasonic bath (BactoSonic14.2, Bandelin GmbH, Berlin, Germany) at a frequency of 42 kHz with a power of 0.22 W/cm^2^. The resulting sonication liquid is then homogenized, and 5–10 mL is centrifuged for 5 min at 2500 rpm. The resulting precipitate will be inoculated onto culture media and incubated at 37 degrees to inspect them for bacterial growth.

### 2.6. Ethics and Personal Data Protection

This study has obtained ethics approvals from the ethical committee of the County Clinical Emergency Hospital of Sibiu and the Lucian Blaga University of Sibiu. To be enrolled in the study, the patient or the legal representative must sign an informed consent. The consent can be withdrawn at any point without impacting the patient’s treatment and care.

According to Romanian law, the information collected for this study will be confidential, and patient data will not be published. Access to personal data is provided only to the research team involved in the study. However, the control committees will be granted access to the initial patients’ data to verify compliance with the study procedures. However, they will not be allowed to make the data public.

## 3. Discussions

Since critically ill patient represents an enormous challenge no matter the admission diagnosis, the primary aim of the healthcare system is to decrease the mortality and morbidity of the patients and shorten the length of stay in intensive care units. By achieving these targets, the total costs of care will be significantly lower. More than other complications, VAP can extend the length of ICU stay and pose the patient with a significant risk of death. Many studies focus on preventing VAP, early diagnosis, and targeted treatment. 

At this point, though, there is no prophylactic measure that is 100% efficient, and the rapid diagnostic methods (PCR methods for bacterial isolation) are not readily available in all intensive care units. This is the main reason for using sonication as a new prevention and early diagnosis method. Sonication is cheap, and there is no need for highly trained personnel or expensive reactants. This kind of method was used in clinical practice sparingly. Dentistry is the main branch that uses sonication to determine the bacteria in the biofilms of dental prostheses. In the last years, though, steps in using sonication were made in orthopedy, when this method was used to isolate bacteria from infected hip or knee prostheses. Because the traditional methods could not isolate any microorganism, the biofilm was dislodged with the help of the ultrasounds, and a rare bacteria were isolated: Ralstonia pickettii. The patient with a hip infection with R. picketii could be treated with targeted antibiotics after the bacteria responsible for the infection was finally isolated [30].

As this method progressed in orthopedy, more doctors used sonication to isolate bacteria on the infected knee and hip prostheses. In a recent study, the authors isolated many strains of bacteria. There were found gram-positive bacteria and also gram-negative bacteria with different kinds of resistance to antibiotics. Though the clinical signs and symptoms suggest prosthetic infection, no microorganism could be isolated through classic methods. Using sonication on infected hip or knee prostheses extracted from patients, the authors isolated numerous strains of microorganisms: Coagulase-negative staphylococci (CoNS) species—epidermidis, lentus, xylosus, epidermidis, hominis, hemolyticus; Enterococcus faecalis, Escherichia coli, Klebsiella spp, Proteus mirabilis, Pseudomonas spp and even Acinetobacter spp. Along with sonication, other tissue samples were collected in the intraoperative period: one was used for the histopathological examination, the prosthetic membrane, and the others were sent for bacterial cultures in the microbiology laboratory [31].

For orthopedic patients, to use sonication on the prosthesis, there is a need for genuinely invasive procedures. On the other hand, the invasivity is very low in dentistry, at least in the case of totally mobile dental prostheses. In the intensive care unit, we are between orthopedy and dentistry to get the specimen for sonication, as a piece of the intubation cannula is needed.

As with any diagnostic method, sonication has its limitations. First, the sonication fluid is needed. If the patient is not stable enough (there are difficulties in maintaining proper oxygenation or the cardiovascular system needs increasing vasoactive or positive inotrope support), the tracheal cannula cannot be changed in the proposed timeline without endangering the ill. In this scenario, the cannula will stay on the spot, and the patient will be excluded from the study. Even though it enhances detection sensitivity compared to traditional culture methods, it may cause cell damage and loss of viability, and furthermore, cannot differentiate between viable or nonviable microorganisms.

Another area for improvement regarding this study is the impossibility of isolating certain species of bacteria. Bacteria that require special growth media can be included in this category: atypical bacteria, mycobacteria, and anaerobic bacteria. It has already been described in the medical literature that mycobacteria have the ability to adhere to surfaces and form biofilms [32]. The ultrastructure of the mycobacterial biofilms has been studied through different kinds of methods: Confocal laser scanning microscopy (CLSM) combined with fluorescent dyes, Nile Red, or LIVE/DEAD BacLight. This type of coloration is used to differentiate between the mycobacterial species by analyzing the phenotypic characteristic of biofilms (growth rate, live and dead bacteria, autofluorescence) [33]. Most anaerobes adhere strongly to surfaces, as G. Donelli and Co concluded after studying biliary stents biofilms. Furthermore, they discovered that a plurimicrobial biofilm is even more adherent than the monomicrobial one, so the energy of the sound wave used for the dislodgement should be higher. After the dislodgement, the bacteria were grown on specific media brain heart infusion (BHI) broths and then colored with Hucker crystal violet. The colored and then dried plates were examined by using microplate photometers. Even further, field emission scanning electron microscopy (FESEM) or confocal laser scanning microscopy (CLSM) was used [34]. As there are methods described in the literature to evaluate biofilm formation and composition, most of them are expensive and difficult to use. They cannot be used as a bedside method and are not readily available for all intensive care units or hospitals worldwide.

The proposed number of patients to be included in the study is at least 100. This figure might not be achieved if the number of intubated and ventilated patients in our ICU is lower than the number proposed or if other exclusion criteria are met on the way (withdrawn consent, less the 48 h of mechanical ventilation).

The possible upgrades of the current study can also be added if it contained a sub-study about antibiotic activity on the biofilm of the intubation cannula as compared to the antibiotic activity on the bacteria isolated from the tracheobronchial secretions. Furthermore, it is essential to know the difference between the minimal inhibitory concentration (MIC) of the two types of bacteria. The literature has already published that the antimicrobial concentrations needed to sterilize biofilms are more significant than those needed to eradicate the same bacteria in a planktonic state [35]. It is well known that bacteria contained in biofilms have overwhelming survival capabilities to multiple classes of usual antimicrobials [36,37], even when it is not considered the microorganism’s MDR status. Knowing this, the patients can be treated accordingly, using the appropriate doses of antibiotics in this subtype of population: the infected critically ill patient admitted to the intensive care unit.

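### A patient too unstable for a scheduled tube change is dropped from the whole study, although only that cannula specimen is unavoidably lost

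*Protocol article*

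**What the plan says.** **The rule.** Section 3 (Discussions) describes a patient whose oxygenation is hard to maintain, or who needs rising vasoactive or inotropic support, so that the tube cannot safely be changed on schedule. It then states: "In this scenario, the cannula will stay on the spot, and the patient will be excluded from the study". Section 2.3 carries the same ground as an exclusion criterion, "Clinically unstable patients, so the samples could not be collected", and adds a second one for specimens: "The non-compliant collection of biological samples in patients".

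**The schedule (section 2.5).** T0 is a "tracheal aspirate collection in the first 2 h after" ICU admission or intubation. A second aspirate follows at 48–72 h, together with the first tube change: "Replacement of the endotracheal cannula at 48–72 h from T_0_ and collection of a cannula specimen". A third aspirate is due at 168–192 h "if the patient requires prolonged mechanical ventilation or required reintubation less than 24 h from the time of extubation". A second tube change falls in the same window.

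**The aims (section 2.1).** One aim is "Determination of the optimal time to replace the intubation cannulae in patients that need mechanical ventilation for more than 48 h", with no restriction to patients who can be exchanged. Another is that "it should be determined whether a clean cannula with a sterile biofilm can prevent the onset of VAP". Section 2.4 also collects 28-day mortality.

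**The concern.** Fitness for exchange is not a baseline property. It becomes known two to eight days after T0, and it reflects how the patient has fared since. A rule that removes the whole patient at that point selects on post-baseline course.

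What goes with the patient does not depend on a tube change at that visit: the aspirates, any earlier cannula specimen, VAP status and 28-day mortality. Patients with worsening oxygenation or rising circulatory support would be missing from those results. The results would then describe a more stable group than the one named in section 2.1.

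There is also a possible link with an outcome of interest. Oxygenation trouble is one ground for exclusion in the Discussions section. Falling oxygenation is one of the VAP signs in the Introduction, which also dates VAP from 48 h of ventilation, when the first exchange window opens. The overlap is partial, because VAP needs radiological and other criteria as well.

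**Working it through.** The plan gives no share of unfit patients and no calculation on this point, so there is no figure to reproduce. The check is mainly a reading of the rule against the schedule.

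**1. Timing.** The T0 aspirate is taken within 2 h. The exchanges are at 48–72 h and 168–192 h. A judgement that the tube cannot be changed on schedule must therefore follow T0 sampling. Section 3 separately foresees exclusion criteria being met during the study. Its examples are withdrawn consent and short ventilation, so that sentence supports the timing and not the instability rule itself.

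**2. What is lost for each excluded patient.**

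| Unfit at | Unavoidably missing | Lost only because of the rule |
|---|---|---|
| 48–72 h | first cannula specimen | up to 2 aspirates, VAP status, 28-day mortality |
| 168–192 h | second cannula specimen | up to 3 aspirates, VAP status, 28-day mortality and, read literally, the first cannula specimen |

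The text does not say whether a patient unfit at 168–192 h keeps the 48–72 h data. The third aspirate is already conditional, so patients with only the first set of samples are foreseen anyway.

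**3. What rewording cannot recover.** Let p be biofilm positivity among exchanged patients and f the share not exchanged. Positivity among all ventilated patients then lies between p(1−f) and p(1−f)+f, a width of f. With p = 50% and f = 20% (both assumed) this is 0.50 × 0.80 = 40% to 40% + 20% = 60%. The width is the same whether or not unfit patients stay in the study, so it does not measure the harm of the rule.

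**4. What the rule could do to an outcome.** Let u be the share excluded, and let the outcome rate be p_s in exchanged and p_u in excluded patients. The observed rate minus the all-patient rate is p_s − [(1−u)p_s + u·p_u] = u(p_s − p_u). All inputs here are assumed.

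- p_s = p_u: 0 points.
- 20% against 40%: −2.0, −4.0 and −6.0 points at u = 10%, 20% and 30%.
- 9% against 40% (the ends of the VAP range in the Introduction, borrowed only as a wide contrast): −3.1, −6.2 and −9.3 points.

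**5. Is the direction fixed for VAP?** Let v be the VAP share, and let e_V and e_0 be the exclusion rates with and without VAP. The retained share is v(1−e_V) / [v(1−e_V) + (1−v)(1−e_0)]. Take v = 9% or 40% from the Introduction, and assume the exclusion rates.

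- e_V = 30%, e_0 = 10%: 0.063/0.882 = 7.1%, or 0.28/0.82 = 34.1%.
- e_V = e_0: no shift.
- e_V = 10%, e_0 = 20%: 0.081/0.809 = 10.0%, or 0.36/0.84 = 42.9%.

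The shift can go either way. The document supplies neither exclusion rate, and its 9–40% refers to intubated patients in general, not to those ventilated beyond 48 h.

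**The case against.** **No tube, no specimen.** A reader might infer that the rule is what confines the replacement-time aim to exchangeable patients. The documents do not support that. A tube left in place yields no scheduled specimen under any rule, and the comparison of biofilm with secretions needs both samples. This objection stands in full. It narrows the point to the data that could have been kept.

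**It works like an entry criterion.** Inclusion requires more than 48 h of ventilation, so eligibility is settled only as the first window opens, and every T0 aspirate is provisional until then. This has weight at 48–72 h. It does not help at 168–192 h, when the patient is already in the study and may have given a cannula specimen. Nor does it square with an aim worded for everyone ventilated beyond 48 h.

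**The VAP link is speculative.** It rests on one shared sign, and Group 1 patients are ventilated for pulmonary infection already, so VAP onset is a different question for them. A reader might infer that VAP will be under-counted. The calculation shows that the sign is open, so that inference fails.

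**It is disclosed, and counts belong elsewhere.** The Discussions section presents the exclusion as a practical limit of needing the specimen. It does not discuss selection or narrow the aim, so disclosure does not cure the rule. A count of unfit patients by time point is reporting detail that an article may leave to the full protocol or the results paper, and its absence is not part of this point.

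**It protects patients.** It does, and the safeguard should stay. A reader might also suspect that the rule hides harm from tube changes. The text describes a decision taken before any attempt, so it gives no ground for that.

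**Conclusion.** The point holds in a limited form. Sections 2.3 and 3 state a rule, reversed nowhere in the document, that removes a patient from the whole study on the strength of clinical course after T0. The missing cannula specimen is unavoidable. The loss of aspirates, VAP status and 28-day mortality is not, and neither is the loss of the first cannula specimen of a patient unfit at 168–192 h, if the rule is read literally.

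Outcomes would therefore describe a group selected for stability, while section 2.1 words its replacement-time aim for all patients ventilated beyond 48 h. The size and direction of any bias cannot be derived from the document. In the assumed scenarios an outcome rate moves by 0 to about 9 points, and for VAP the sign can reverse. These figures show sensitivity only.

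This is a cheap improvement to an observational study and not a fault that invalidates it.

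**What to change.** Keep the stability safeguard exactly as it is, and make two changes.

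1. Replace the whole-study exclusion in section 3, and the two matching criteria in section 2.3, with wording such as: *If the cannula is not changed at a scheduled time, or the specimen is unusable, the patient is left out of the biofilm analysis of that time point only. Tracheal aspirates, earlier specimens and outcomes are kept.* This also settles what happens to the first-exchange data of a patient unfit at 168–192 h.
2. Limit any conclusion on replacement time under section 2.1 to patients judged stable enough for exchange. Rewording the exclusion cannot widen that group.

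The cost is three reworded statements, continued aspirate and outcome recording for patients who would otherwise have left, and incomplete specimen sets to handle in the analysis. The conditional third aspirate in section 2.5 already implies such sets. No extra tube change or other new procedure is needed, and the safety decision is unaffected.
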